#### Sensitivity analyses

Alternative parameterisations of the study outcomes will be considered. For the prescribing rate of antimicrobials with courses longer than 7 days (objective 2), we will consider total days of therapy (with the number of prescriptions as the offset) as an alternative outcome using a zero-truncated negative binomial model. There may be issues with how indications are coded in the electronic medical record, whereas the type of antimicrobial prescribed is very likely to be accurate. A sensitivity analysis will be performed using the prescribing rates (for all visits) for antimicrobials most often prescribed for viral respiratory conditions (eg, amoxicillin, amoxicillin/clavulanic acid, azithromycin^37^) as the outcome, rather than the indication-specific prescribing rate of antimicrobials for viral respiratory conditions. Since acute respiratory tract infections make up a large proportion of total antimicrobial prescribing, the signal from the intervention may be evident using these outcomes as well.

To ascertain whether there could be negative effects of the stewardship intervention, we will evaluate (1) the frequency of bacterial pneumonia and pyelonephritis diagnoses and (2) the number of hospital admissions (including those related to infection) in the pre-intervention and post-intervention periods. Admissions data are only available for CHS (Israel), and thus will only be evaluated at this site only.

Including patient composition as predictors (eg, percentage of patients 65 and older, percentage of female patients) may be insufficient to capture differences in prescribing occurring between strata of age and sex. A sensitivity analysis will be performed where the outcome will be stratified by age group and sex and modelled separately. Although stratification increases the noise in each individual time-series, these models may reveal differences in the effectiveness of the intervention across sex/age groups, which have different prescribing patterns.

As the offer to enrol in the study is randomised at one study site (Southern Israel), an intention-to-treat analysis will be performed as a supplementary analysis at this site only. The characteristics and prescribing patterns of responders and non-responders among those offered enrolment will also be compared.

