#### Covariates

The analysis will include potential predictors of a provider’s baseline prescribing rate, as well as seasonality (table 2). These include a provider’s age, sex and employment status (full-time or part-time),^10^ and monthly practice patient composition (by age and sex).^19 32^ We will also use nested random intercepts for provider, practice group (clinic) and study site, representing within-group prescribing norms and a provider’s baseline willingness to prescribe after accounting for other predictors, as well as heterogeneity between study sites. Seasonality will be accounted for using a categorical variable for each month compared with January. An interaction term with study site will be included for each covariate to allow for differences in seasonal and demographic prescribing patterns between the two countries in our study.

**Table 2 T2:** Covariates included in the interrupted time-series analysis of the OPEN Stewardship Study

Variable	Purpose	Form	Description
Number of prescriptions	Outcome	Integer	Number of antimicrobial prescriptions for given indication
Number of visits for indication	Offset	Integer	Number of patient visits for given indication
Study site	Covariate	Binary	Southern Israel versus Ontario, Canada (baseline)
Practice group	Random intercept	ID	Random intercept for practice group (nested within region)
Provider	Random intercept	ID	Random intercept for provider (nested within practice group)
Month	Covariate	Categorical	Calendar month (baseline=January)
Month×study site	Interaction	Interaction	Allows different value for coefficients for Southern Israel
Physician age	Covariate	Integer	Physician age at *t_−12_*
Physician age×study site	Interaction	Interaction	Allows different value for coefficient for Southern Israel
Physician sex	Covariate	Binary	Female versus male (baseline)
Physician sex×study site	Interaction	Interaction	Allows different value for coefficient for Southern Israel
Physician employment status	Covariate	Binary	Part-time versus full-time (baseline)
Physician employment status×study site	Interaction	Interaction	Allows different value for coefficient for Southern Israel
Percent female patients	Covariate	Continuous	Percentage of visits by female patients
Percent female patients×study site	Interaction	Interaction	Allows different value for coefficient for Southern Israel
Percent patients 17 and under	Covariate	Continuous	Percentage of visits by patients 17 and younger

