**Figure 2 F2:**
[figure not shown]
Pre-intervention and post-intervention periods for objectives 1–4 of the OPEN Stewardship Study. (A) Objective 1, overall prescribing (report sent at *t_0_*). (B) Objective 2, prescribing with duration longer than 7 days (report sent at *t_0_*). (C) Objective 3, prescribing for viral respiratory conditions (report sent at *t_3_*). (D) Objective 4, prescribing for acute sinusitis (report sent at *t_6_*). *t_0_* represents the time of the first report (intervention); *t_−12_* represents 1 year prior to the first report; *t_12_* marks the conclusion of the study period (1 year after the first report).

**Table 3 T3:** Timing of analyses for objectives 1–4 of the study

Objective	Outcome	Unit of analysis	Intervention time	Number of observations in intervention cohort		Total observations/observations in control cohort
				Pre-intervention	Post-intervention	
1	Prescribing for all indications	Provider	*t_0_*	12	12	24
2	Prescribing (for all indications) with duration longer than 7 days	Provider	*t_0_*	12	12	24
3	Prescribing for viral respiratory conditions	Provider	*t_3_*	15	9	24
4	Prescribing for acute sinusitis	Provider	*t_6_*	18	6	24

The definitions of the pre-intervention and post-intervention periods are dependent on the delivery time of the report (intervention) related to each objective.

The intervention effect will be modelled as a level change and/or change in slope for the prescribing rate at the beginning of the post-intervention period.^26^ An interaction term with study site will be included to allow for differences in the intervention effect between Ontario and Southern Israel. A key assumption of interrupted time-series analysis is that the pre-intervention time trend is assumed to be linear, which must be evaluated through visualisation.^34^ Otherwise, non-linear terms may be considered. Model fit can be assessed by comparing models containing intervention parameters to a null model not containing intervention parameters using a statistic such as Akaike information criterion.

Autocorrelation in each provider’s time-series should be accounted for by the random intercept (provider nested within practice group nested within study site) and by controlling for seasonality (categorical variable for month).^26^ In case autocorrelation is present in the residual distribution, an autoregressive covariance structure will be considered.

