#### Sample size

We provide an approximate sample size calculation for a difference in antimicrobial prescribing between two groups (intervention and control) in a Poisson framework using the method described by Whitehead^38^ and implemented in an online calculator (http://www.obg.cuhk.edu.hk/ResearchSupport/StatTools/SSiz2Counts_Tab.php). In Fleming-Dutra *et al’s*^8^ study of outpatient prescribing, 12.6% of visits resulted in an antimicrobial prescription. Since most visits would only result in a single antimicrobial prescription, we take this as the baseline prescribing rate (0.126/visit). The American Academy of Family Physicians estimated in 2012 that their members had an average of 92 patient encounters per week (368 per month).^39^ We define a 15% reduction in prescribing rate as clinically meaningful (0.107/visit). To achieve a power of 90% (with α=0.05, one-tail), we would require approximately 15 physicians in each group to be observed for 1 month each, which is much smaller than our expected sample size at each study site. While the clustering and likely overdispersion of prescribing rates in our sample would decrease our power, the fact that we will have 24 months of observations for each provider (rather than 1 month), as well as pre-intervention and post-intervention observations, greatly enhances the power of our study to detect an intervention effect.

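### Separate models by patient age and sex are expected to show where the intervention works better, but they give no estimate, interval or test of a difference between strata

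*Protocol article*

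**What the plan says.** The Sensitivity analyses section of the protocol article first argues that patient composition, entered as predictors, may not capture prescribing differences between age and sex strata. It then fixes the remedy, a sensitivity analysis with the outcome "stratified by age group and sex and modelled separately". It adds a second use for the same fits: "these models may reveal differences in the effectiveness of the intervention across sex/age groups, which have different prescribing patterns". The drawback is acknowledged in the same sentence: "Although stratification increases the noise in each individual time-series".

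For the other effect modifier, study site, the Statistical analysis section takes a different route: "An interaction term with study site will be included to allow for differences in the intervention effect between Ontario and Southern Israel". Table 2 (Covariates) accordingly crosses Post-intervention and Time×post-intervention with study site. Patient sex and age enter Table 2 only as monthly percentages of visits, each with a site interaction. None is crossed with an intervention term. The stratified fits are therefore the only look at effect differences by patient group that the article states.

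**The concern.** A model fitted to one stratum answers whether prescribing changed in that stratum. Whether it changed more in one stratum than in another is a different question. Its answer is a contrast with its own standard error, and a set of separate fits does not produce one.

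Two things follow if the fits are used to describe who benefits:

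- Stratum results placed side by side, by significance or by point estimate, can look different when the true effect is the same everywhere.
- A contrast computed afterwards from separate coefficients needs their covariance. Nearly every provider contributes visits to several strata, so the covariance is unlikely to be zero, and separate fits do not supply it.

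At stake is an unsupported statement about the patient groups in which the intervention works. The risk is greatest where data are thinnest, for example acute sinusitis, with 6 post-intervention months in Table 3.

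**Working it through.** **The plan's own figure.** The Sample size section sets the error rates: "To achieve a power of 90% (with α=0.05, one-tail", with rates of 0.126 and 0.107 per visit and 368 visits per physician-month. Visits per group = (1.645 + 1.282)² × (0.126 + 0.107) / (0.126 − 0.107)² ≈ 5,527, and 5,527 / 368 = 15.02. The stated figure of about 15 physicians per group reproduces. It is a figure for the whole sample over one month, before clustering and overdispersion. The article acknowledges both without quantifying them, so power within an age-sex stratum cannot be obtained from it. Power is therefore varied below as an assumption.

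**Number of strata (assumed).** The article does not state it. Table 2 has one covariate described as "Percentage of visits by patients 17 and younger" and another for patients 65 and older, which leaves 18–64 as a third group: 3 age groups × 2 sexes = 6. Two strata (sex alone) and three (age alone) are shown as well.

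**Mixed significance under an identical true effect.** With k independent strata and power π in each,

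P(some significant, some not) = 1 − π^k − (1 − π)^k.

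For π = 0.8 and k = 2: 1 − 0.64 − 0.04 = 0.32. For k = 6: 1 − 0.2621 − 0.0001 = 0.738.

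| Assumed power per stratum | 2 strata | 3 strata | 6 strata |
|---|---|---|---|
| 50% | 50% | 75% | 97% |
| 80% | 32% | 48% | 74% |
| 90% | 18% | 27% | 47% |
| 99% | 2% | 3% | 6% |

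**Relaxing independence.** Stratum test statistics were simulated with a common correlation (200,000 runs, 5% two-sided critical value). The correlation values are assumptions.

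| Power per stratum | Correlation | 2 strata | 6 strata |
|---|---|---|---|
| 80% | 0.3 | 27% | 60% |
| 80% | 0.6 | 20% | 45% |
| 50% | 0.3 | 40% | 84% |
| 50% | 0.6 | 29% | 64% |

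Positive correlation lowers the frequency of mixed results but does not remove it.

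**A direct test of the difference.** Under the same identical effect, with independent strata, a joint heterogeneity test at the 5% level rejected in 5.0% of 200,000 simulated trials.

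**Contrasting separate coefficients as if independent.** The variance of a difference is V₁ + V₂ − 2C. With equal variances and correlation ρ, the naive standard error exceeds the correct one by the factor √(2 / (2 − 2ρ)) = 1/√(1 − ρ). For ρ = 0.3 this is 1/√0.7 = 1.20. For ρ = 0.6 it is 1/√0.4 = 1.58. The naive interval is then too wide, so real differences are more easily missed.

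**The case against.** The strongest reply has four parts.

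1. **Purpose.** The section's first reason for stratifying is that composition covariates may be inadequate. Separate fits answer that well, because each stratum gets its own seasonality, trend and dispersion. Effect differences come second and are hedged. This stands, and it is why the point is limited to the second use.

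2. **No rule is written.** A reader might infer that the authors will take significance in one stratum and not in another as evidence of a difference. The article contains no such rule. When it compares models for durability of effect, in Statistical analysis, it speaks of contrasting coefficients. So the percentages above show what would happen under one way of reading the results and do not describe a stated plan.

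3. **Direction of the error.** A reader might also infer that ignoring the shared providers produces false claims of benefit. With positive correlation the opposite holds for a formal contrast: it is conservative. This stands too. The loss is then precision and power.

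4. **Detail for an analysis plan.** How stratum estimates are contrasted is often settled in a document that is not shown here. This stands only in part. The article does more than leave the method open: it names one and gives it a comparative task that it cannot do alone, while for study site it uses an interaction.

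**Conclusion.** The point holds as a minor one. For the stated aim of finding differences in effectiveness across sex and age groups, separate fits provide no estimate, interval or test of those differences, and the covariance needed to build one afterwards is not available from them.

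The size is conditional. It rests on assumed power per stratum, an assumed 2 to 6 strata, assumed independence or correlation, and a comparison by significance that the article does not prescribe. Under those assumptions mixed results under an identical effect run from 32% to 74% at 80% power with independence. For 6 strata at that power they are about 45–60% with correlation 0.3–0.6. They are 2% to 6% if every stratum has 99% power and strata are independent. The documents do not support saying that strata will often disagree, because they do not allow power per stratum to be worked out.

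This is a sensitivity analysis. Objectives 1 to 4 and the sample size do not depend on it.

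**What to change.** Keep the separate fits as a display if wanted; they serve the composition-adjustment purpose. Base any statement about effect differences on one model of the stacked provider-month-stratum counts, with stratum visits as the offset and:

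- stratum effects with stratum-specific month and time terms, so that different seasonality or secular trends are not read as effect modification;
- sex and age-group interactions with both Post-intervention and Time×post-intervention, since Table 2 models a level change and a slope change;
- provider and practice random effects, with provider-clustered (or equivalent) standard errors, because a shared random intercept alone captures correlation in level but not in response to the intervention.

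Report the differences with intervals and one joint test each for sex and for age group, labelled exploratory.

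**Cost.** The model uses the same stratified counts that the separate fits need. It is larger, with more parameters, and may need simplifying for the sparser indications. No new data collection and no change to the primary analysis are required.

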#### Sample size

We provide an approximate sample size calculation for a difference in antimicrobial prescribing between two groups (intervention and control) in a Poisson framework using the method described by Whitehead^38^ and implemented in an online calculator (http://www.obg.cuhk.edu.hk/ResearchSupport/StatTools/SSiz2Counts_Tab.php). In Fleming-Dutra *et al’s*^8^ study of outpatient prescribing, 12.6% of visits resulted in an antimicrobial prescription. Since most visits would only result in a single antimicrobial prescription, we take this as the baseline prescribing rate (0.126/visit). The American Academy of Family Physicians estimated in 2012 that their members had an average of 92 patient encounters per week (368 per month).^39^ We define a 15% reduction in prescribing rate as clinically meaningful (0.107/visit). To achieve a power of 90% (with α=0.05, one-tail), we would require approximately 15 physicians in each group to be observed for 1 month each, which is much smaller than our expected sample size at each study site. While the clustering and likely overdispersion of prescribing rates in our sample would decrease our power, the fact that we will have 24 months of observations for each provider (rather than 1 month), as well as pre-intervention and post-intervention observations, greatly enhances the power of our study to detect an intervention effect.

### Objective 5: survey of usability among participating providers

#### Study design

Physicians enrolled in the antimicrobial stewardship intervention will receive three short surveys to assess the usability of the reports received and to provide feedback on the intervention.

#### Surveys

Surveys will be delivered by email to participants in the intervention group 3 days after the initial receipt of each report using Qualtrics (Qualtrics, Provo, Utah, USA) in Southern Israel and RedCAP^40^ survey software in Ontario (due to differences in institutional policies regarding data collection). The report will be resent with the survey and the recipient will be given 7 days to respond. If the recipient fails to respond within this allotted time, the survey and report are resent again, giving the recipient an additional 7 days to respond. The first two surveys focus on the usability and usefulness of the emailed reports, with additional space for free text feedback. The final report adds additional questions to assess how often they would prefer to receive reports and whether particular additional features would be of use to him or her. Survey questions are given in English in online supplemental appendix 1; translated questions in Hebrew are given in online supplemental appendix 2. Questions were developed in accordance with experts at the Public Health Agency of Sweden. Questions were pilot tested and revised according to the protocol and interviewer guide in online supplemental appendix 3.

#### Statistical analysis

Participants’ attitudes regarding the overall usefulness of the intervention and the informativeness of the figure included in each intervention (table 1) will be assessed in each survey and compared longitudinally with a multilevel linear model. Responses to other questions may be analysed using ordinal regression and/or multinomial regression.

## Ethics and dissemination

The following ethics committees reviewed and approved this study: University of Toronto Research Ethics Board (REB) (Canada), St. Michael’s Hospital REB (Canada), Toronto East Health Network REB (Canada) and Clalit REB (Israel). The veterinary study was further reviewed and approved by: University of Guelph REB (Canada) and Internal Research Review Committee of the Koret School of Veterinary Medicine–Veterinary Teaching Hospital, Hebrew University (Israel).

All patient-level prescribing data will be anonymised prior to receipt, available only as the rate of antimicrobial prescribing per visit, stratified by month and reason for visit (and potentially sex and/or broad age category). Study data will be stored on a secure server and accessible only to study analysts. Study participants from Ontario will be compensated with a gift card. Study participants from Israel will be encouraged to participate by a letter from the chief physician’s office.

The OPEN Stewardship project includes collaborators affiliated with hospitals, universities and public health authorities in four countries. In addition to dissemination through stakeholder networks, the results of this study will be published in an open-access journal and presented at national and/or international meetings.

### Patient and public involvement

Primary care physicians were involved in the conception and design of this study, as well as the study surveys. They were also consulted to assess the appropriate time burden and adequate compensation for participants in the study.
